### Participants

We are recruiting patients of both genders, aged 18 to 75 years who have been diagnosed with major depressive disorder during an acute depressive episode, in accordance with the DSM-5 criteria (Diagnostic and Statistical Manual of Mental Disorders, 5^th^ edition).

The eligibility criteria include the presence of a depressive episode of at least moderate intensity (corresponding to a score ≥ 17 on the 17-item Hamilton Depression Rating Scale, HDRS-17), ability to read and understand Portuguese, at least eight years of schooling and availability to adhere to the study protocol. The exclusion criteria are: 1) other neuropsychiatric conditions, such as bipolar disorder, schizophrenia, substance dependence, dementia, traumatic brain injury, epilepsy and so forth (although participants with anxiety disorders can be included if the primary diagnosis is MDD); 2) high suicide risk (i.e. score > 2 in the Hamilton suicide question); 3) pregnancy; 4) specific contraindications against tDCS, such as electronic or metal implants in the cephalic segment; 5) specific contraindications against escitalopram; 6) severe/life-threatening clinical conditions; or 7) previous participation in other tDCS trials.

Participants will have to be either drug-naïve or drug-free regarding the use of antidepressant drugs (we considered an “antidepressant drug” to be any medication approved for treating MDD by the United States Food and Drug Administration as of the time of onset of the trial). A minimum period of 3 weeks (5 weeks for fluoxetine) will be set aside for drug washout. Benzodiazepine drugs will be allowed, although only at low doses (less than 20 mg/day of diazepam or equivalent). Also, since escitalopram is our active comparator, patients using (or who have used) escitalopram in the current depressive episode will not be included, since they would be escitalopram-resistant.

The adherence strategies for minimizing dropouts include: reimbursement of transportation costs; flexibility in the study schedule; allowance of up to four missed visits during the acute study phase and up to two missed visits during the weekly tDCS phase; reminders for patients regarding their appointments; and offering active tDCS after the endpoint to non-responder patients who received sham tDCS.

### Interventions

We are using Soterix Medical tDCS devices specially customized for our study (Soterix Medical, New York, NY, USA, Model 1x1 tDCS-CT). For tDCS, the anode is placed over the left and the cathode over the right dorsolateral prefrontal cortex. The electrode positioning is based on the “Omni-Lateral-Electrode” (OLE) system, which is a simple, reproducible, and practical method for positioning the electrodes using a headband (Figures 2A and 2B). Moreover, the OLE method optimizes electric current densities across the DLPFC, in comparison with other non-neuronavigated methods for tDCS electrode placement, such as the EEG international 10-20 system and the 5-5 cm rule (Seibt, Brunoni, Huang and Bikson, under review), taking into consideration inter-subject variability in head anatomy (Figure 2C).

**Figure 2. f2:**
[figure not shown]
Electrode positioning in the ELECT-TDCS trial. (A) and (B) The figure shows the placement procedure for the Omni-Lateral-Electrode (OLE) system, which is placed as follows: 1) Select EasyStrap size (small, medium or large); 2) Place the midpoint of the occipital strap over inion (I_z_); 3) Position the hinges that link occipital-, electrode- and chin strap over the most dorsal point on the ear; 4) Adjust the angle between the occipital and electrode straps to 165° and the distance across the scalp between the dorsal electrode edges to 10 cm. Adapted from Seibt, Brunoni, Huang and Bikson (under review). (C) Brain current flow produced in one tDCS session in ELECT-TDCS.

The stimulation parameters are: current intensity of 2 mA, electrode size of 25 cm^2^; session duration of 30 minutes (excluding the fade-in and fade-out periods of 15 seconds); and total number of 22 sessions, with 15 sessions applied consecutively once a day (except for weekends), and after that, seven more sessions applied once per week until the study endpoint at week 10. For operational reasons, these sessions are held on either Tuesdays or Thursdays, according to the patient’s preference and always respecting the one-week interval.

Sham tDCS is delivered using the same procedure as active tDCS, but using a period of only 30 seconds of active stimulation at 2 mA (or an overall active period of 60 seconds, taking into account the 15 seconds for both the fade-in and fade-out periods), with the stimulator remaining active but not generating current for 30 minutes, for the purpose of double blinding. This method, adapted from Gandiga et al.,^33^ has been used in several tDCS protocols^34^ and had the same blinding efficacy as the placebo pill in SELECT-TDCS.^35^ We are using fully automated devices that perform active or sham tDCS according to a randomized stimulation code.

The pharmacological intervention starts simultaneously with tDCS and consists of 10 mg pills of escitalopram oxalate or placebo. Patients receive 10 mg/day of escitalopram/placebo for the first 3 weeks and 20 mg/day for the remaining 7 weeks. Escitalopram was chosen because it is an effective antidepressant treatment with few adverse effects^36^ and its full dose (20 mg/day) is relatively easier to achieve than those of other antidepressant drugs. Thus, maximum dose-up titration can be done in the beginning of the trial. Therefore, we are able to compare tDCS against a full dose of an effective antidepressant without compromising blinding due to adverse effects.

The escitalopram pills are from Libbs (São Paulo, Brazil), a Brazilian pharmaceutical drug company that produces Reconter (escitalopram oxalate), which is a generic drug product comparable to the brand reference Lexapro (Lundbeck Brasil Ltda., Rio de Janeiro, Brazil). In Brazil, all generic drug products have their bioequivalence tested and certified by the Brazilian Health Surveillance Agency (ANVISA). We also independently assessed whether Reconter would be comparable to Lexapro in terms of dosage, strength and quality by testing both drugs in the Clinical Analysis Laboratory of the School of Pharmaceutical Sciences of the University of São Paulo. They achieved the same performance regarding their physical-chemical properties. The School of Pharmaceutical Sciences also produces the placebo pills, which are identical to the Reconter pills in terms of shape, color, weight and taste. Escitalopram and placebo pills are put in identical opaque bottles, identified solely by a number corresponding to the patient’s code. Adherence to the drug intervention will be verified by means of a pill count at the end of the study.

### Procedures

Participants are randomized in accordance with a computer-generated list at www.randomization.com. For allocation, we use opaque sealed envelopes containing the code corresponding to the group assigned for each participant. This code is entered into the tDCS device that automatically delivers either active or sham stimulation.

Diagnoses are made by certified psychiatrists or clinical psychologists and are confirmed through the Mini-International Neuropsychiatric Interview (M.I.N.I.). The data collected include diagnosis subtype (melancholic, atypical or depressive with mixed features), duration of illness and number of failed antidepressant treatments during the current episode. The Hamilton Depression Rating Scale (HDRS-17), the Montgomery-Asberg Depression Rating Scale (MADRS), the Positive and Negative Affect Scale (PANAS) and the STAI (State-Trait Anxiety Inventory) are applied at different time points (Table 1).

**Table 1. f3:**
[figure not shown]
Study schedule for the ELECT-TDCS

To assess adverse effects, we use the Systematic Assessment for Treatment of Emergent Effects (SAFTEE)^37^ and the tDCS adverse events questionnaire.^10^ We apply the Young Mania Rating Scale (YMRS) to assess hypomanic symptoms, which have already been described after tDCS antidepressant treatment.^38^^,^^39^^,^^40^^,^^41^ Also, we include neuropsychological assessments in our study, primarily to verify that tDCS will not be associated with cognitive impairment, using the Montreal Cognitive Assessment (MOCA), the Wechsler Adult Intelligence Scale-III digit span (forward and backward) and digit symbol coding subtests, the Verbal Fluency Test (FAS and animal/fruit categories) and the Trail Making test. The Temperament and Character Inventory (TCI) is being collected at baseline and endpoint to assess the personality traits associated with and modified by the antidepressant treatment. We also assess blinding performance by asking patients to guess their own treatment allocation group at week 3 and at the endpoint, and ask interviewers to make the same guesses regarding these patients’ treatment.

Furthermore, we are investigating several biomarkers, including:

Heart rate variability (HRV), which becomes lower in cases of depression^42^ and possibly reflects the disrupted sympathovagal balance observed in MDD. However, recent evidence suggests that this alteration is primarily driven by the direct effects of antidepressant drug treatment.^43^ In our SELECT-TDCS trial, we did not observe that either tDCS or sertraline changed HRV levels, which were lower than in matched healthy controls.^44^ In ELECT-TDCS, we assess HRV values over a larger timeframe (of 10 weeks) and in a larger sample size.Genetic polymorphisms: (i) The serotonin transporter gene (5HTTLPR, SLC6A4) is related to antidepressant response.^45^^,^^46^ Two out of three rTMS studies also found that it was associated with antidepressant response.^47^^,^^48^^,^^49^ In SELECT-TDCS we also found that it was associated with a larger active-sham difference.^50^ (ii) The 5HT_2A_ receptor gene (rs6311 and rs6313) was associated with a larger active-sham difference^51^ and antidepressant response.^52^ Although a meta-analysis was inconclusive regarding its association with antidepressant response,^46^ it was identified as associated with citalopram antidepressant response in the STAR*D trial.^53^ (iii) TPH1 polymorphism was associated with citalopram antidepressant response in the STAR*D trial. The A allele was associated with lower synthesis of serotonin^54^ and a recent meta-analysis^46^ showed that this allele was associated with worse antidepressant response. (iv) Brain-derived neurotrophic factor (BDNF) polymorphism (rs6265) is a neurotrophin associated with synaptic plasticity.^55^^,^^56^ Two meta-analyses showed that Met/Met and Val/Met were associated with antidepressant response,^46^^,^^57^ while one rTMS study found that Val/Val determined a better antidepressant response.^58^ In SELECT-TDCS, this polymorphism was not associated with antidepressant response.^50^
Motor cortical excitability for tDCS has been used since the reappraisal of tDCS by Nitsche and Paulus in 2000.^11^ Currently, one important line of tDCS research involves measurement of motor cortex excitability after use of tDCS in combination with psychoactive drugs.^59^ This procedure allows indirect measurement of the GABAergic activity (ICI and CSP) and glutamatergic activity (ICF) of the motor system.^60^ These neurotransmitters are involved in the pathophysiology of depression.^61^ Recent studies observed that in relation to healthy subjects, the ICI, ICF and CSP indices are altered in depressed subjects,^62^^,^^63^^,^^64^ although their role as predictors of antidepressant response was not sufficiently investigated.Brain imaging by means of MRI will be collected in approximately half of the sample (120 patients) at baseline and endpoint, and this imaging will include voxel-based morphometry (VBM), diffusion tensor imaging (DTI) and resting-sate functional MRI. Regarding VBM, one consistent finding observed in depressed patients is that the volume of the grey matter in the prefrontal and anterior cingulate cortex bilaterally is lower,^65^^,^^66^^,^^67^ and that there is an increase in gray matter in the left DLPFC after successful antidepressant treatment.^68^ These brain areas will be explored as predictors of tDCS response. On DTI, the fractional anisotropy (FA) of the prefrontal cortex (bilaterally), right temporal lobe and right fusiform gyrus were found to be lower in MDD patients.^69^ Studies on repetitive TMS found an increase in FA in the left frontal-medial gyrus after successful antidepressant treatment,^70^^,^^71^ and these regions are explored in our study. For resting-state fMRI, we explore changes in the default-mode network (DMN) and anticorrelated network (AC) after tDCS treatment. Previous studies observed that depressed patients present greater DMN activity and lower AC activity^72^ and that antidepressant treatment can change the brain activity of these regions.^73^
BDNF levels in blood are lower in depressed subjects than in healthy subjects and increase after successful pharmacological treatment.^74^^,^^75^ Nonetheless, recent meta-analyses showed that ECT increases BDNF levels in blood, but not rTMS or tDCS.^76^^,^^77^ The possible explanations for this are the low number of rTMS/tDCS studies that used non-optimal treatment protocols and the lower period of observation between measurements. In ELECT-TDCS, BDNF levels in blood are assessed at baseline, week 3 and the endpoint.

### Design and sample size determination

ELECT-TDCS uses a non-inferiority, triple-arm, placebo-controlled design, with 3:3:2 permuted block randomization in which participants are respectively assigned to escitalopram, tDCS or placebo. Our aim is to prove that tDCS is non-inferior (i.e. that it has similar or superior efficacy) to escitalopram. The placebo group is used for the following purposes. (1) To ensure assay sensitivity. The placebo ascertains that a similar result between escitalopram and tDCS occurred not due to a false-positive finding caused by methodological issues such as insufficient sample size, sample bias, poor blinding, etc., but in fact due to true equivalence between treatments. (2) To allow direct (superiority) comparisons between the pharmacological treatment and placebo, which is critical, since up to 50% of antidepressant drug trials fail to detect superiority between the active treatment and placebo.^78^ (3) To allow direct comparisons between the experimental treatment and placebo, given that evidence of tDCS efficacy is still being established. (4) To avoid setting up an arbitrary efficacy margin, which would be a problematic approach because the active comparator in the trial will not necessarily have the same efficacy as previous findings in the literature.^79^ For these reasons, the non-inferiority design with a placebo group is considered to be the gold standard for this type of trial according to the US Food and Drug Administration (FDA) and the European Medical Agency (EMA).^80^

The M_2_ margin (relative efficacy of the experimental treatment to the active comparator) is based on a fraction retention factor (*f)* of the M_1_, given that the relative efficacy of the experimental treatment to the active comparator could only be larger than the efficacy with placebo if the active comparator is worse than placebo. The fraction retention varies according to the condition investigated: for instance, in studies focusing on vaccines and oncology, the *f* value should be close to 1; whereas for chronic and functional disorders, this value ranges between one-half and one-third.^31^^,^^79^ There is no consensus regarding the *f* value in non-inferiority trials for MDD, although Nutt et al.^81^ proposed that for generalized anxiety disorder, the value should be 50%. In this trial, we adopted the *f* value of 50%, based on Nutt et al.^81^ and considering that MDD is comparable to generalized anxiety disorder with regard to methodological aspects (large placebo response, short duration of clinical trials, similar pharmacological treatments, comparable scales etc.).

Therefore, in our trial, M_2_/M_1_ = 0.5, although M_1_ is based on the difference between the active comparator and placebo and it will be known only when the study has been finished. Although this approach indexes the relative efficacy of tDCS versus escitalopram according to the placebo response of the study, it is theoretically possible that the escitalopram-placebo difference is too large, thus producing a large M_2_ value that could favor a finding that comparison between escitalopram and tDCS does not show any significant difference, even if escitalopram clinically outperforms tDCS. To avoid this issue, we will only consider that tDCS was non-inferior to escitalopram if the mean difference between escitalopram and tDCS is less than 3 points on the HDRS-17. The threshold of 3 points was chosen considering the National Institute for Health and Clinical Excellence (NICE) guidelines, which establish that this is a clinically meaningful difference in efficacy.^82^

To determine the sample size, we first needed to establish the randomization proportions between the groups. Pigeot et al.^31^ recommended a 1:1:k_p_ ratio, where k_p_ is determined according to the fraction retention factor, as shown below:

$$k_{placebo}\;=\;\left[(1\;-\;f)\;\surd 2\;+\;2f\right]/(1\;+\;f^{2})$$

According to this formula, for *f* = 0.5, k_p_ is 0.69. Therefore the optimal proportion for allocation between the groups is 1:1:0.69, or approximately 3:3:2, as used in ELECT-TDCS.

We estimated our sample size in accordance with the suggestion of Pigeot et al.^31^ for non-inferiority, triple-arm trials:

$$N_{arm}\geq {\left(t_{1-\alpha ,\;3n-3}\;+\;t_{1-\beta ,\;3n-3}\right)}^{2}*(1+f^{2}+{\left(1-f\right)}^{2})\;{*\left[\left(\sigma /\;{µ}_{DRUG}-{µ}_{PLACEBO})/(r-f\right)\right]}^{2*}$$

This formula shows that the sample size is a product of three factors (in parentheses). The factor in the first parentheses take into account the values of α and β, which were, respectively 0.025 (one-tailed) and 0.2. The factor in the second parentheses is the *f* value (the higher the *f* value is, the larger the necessary sample size will be), which was determined as 0.5 for our study. The factor in the last parentheses involves the standard deviation and effect sizes of the interventions. We took the value of the standard deviation to be a function of the difference in efficacy between the active comparator and the placebo:^31^

$$\sigma =\varepsilon \;({µ}_{DRUG}-{µ}_{PLACEBO})$$

The ε value indicates that the standard deviation is associated with the mean difference values observed in the study. It ranges from 0.2 to 2, and values > 1 are considered conservative. In the present study, we took the ε value to be 1.5, i.e. the standard deviation would be 1.5 times the value of the difference in efficacy between the active intervention and the placebo, which is compatible with depression studies in which the variance is usually high.^†^

Therefore, considering an attrition rate of 13% (similar to SELECT-TDCS), β = 0.2, α_one-tailed_ = 0.025, *f* = 0.5 and ε = 1.5, a total sample of 240 patients will be necessary in order to reject our null hypothesis. For 3:3:2 randomization, this means that in the end, 90, 90 and 60 patients will be respectively allocated to the tDCS, escitalopram and placebo groups.

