**METHODS::**

ELECT-TDCS compares the efficacy of active tDCS/placebo pill, sham tDCS/escitalopram 20 mg/day and sham tDCS/placebo pill, for ten weeks, randomizing 240 patients in a 3:3:2 ratio, respectively. Our primary aim is to show that tDCS is not inferior to escitalopram with a non-inferiority margin of at least 50% of the escitalopram effect, in relation to placebo. As secondary aims, we investigate several biomarkers such as genetic polymorphisms, neurotrophin serum markers, motor cortical excitability, heart rate variability and neuroimaging.

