**RESULTS::**

Proving that tDCS is similarly effective to antidepressants would have a tremendous impact on clinical psychiatry, since tDCS is virtually devoid of adverse effects. Its ease of use, portability and low price are further compelling characteristics for its use in primary and secondary healthcare. Multimodal investigation of biomarkers will also contribute towards understanding the antidepressant mechanisms of action of tDCS.

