## METHODS

### Overview

The ELECT-TDCS trial randomizes patients into: sham-tDCS/placebo-pill (placebo group), sham-tDCS/escitalopram (escitalopram group) and active-tDCS/placebo-pill (tDCS group). It was approved by the Local and National Ethics Committee (CAAE:10173712.3.0000.0076) of the University Hospital and Clinics Hospital of the University of São Paulo and is registered in clinicaltrials.gov (NCT01894815). All study participants provide written, informed consent for participation in the study.

Our null hypothesis is that the improvement, i.e. the difference in efficacy between baseline and endpoint measurements of the tDCS group (µ_tDCS_) will be less than or equal to 50% (retention fraction *f* ≤ 50%) of the difference in the improvement between escitalopram and placebo (µ_drug_ - µ_placebo_). The study’s primary aim is to prove the alternative hypothesis, i.e. that this difference is greater than 50% (*f* > 50%).

$$H_{o}:\;{µ}_{tDCS}\;-\;{µ}_{placebo}\;\leq \;50\%\;({µ}_{drug}\;-\;{µ}_{placebo})$$

*or*

$$H_{o}:\;{µ}_{tDCS}\;-\;0.5\;{µ}_{placebo}\;-\;0.5\;{µ}_{drug}\;\leq \;0$$

$$H_{A}:\;{µ}_{tDCS}\;-\;{µ}_{placebo}>\;50\%\;({µ}_{drug}\;-\;{µ}_{placebo})$$

*or*

$$H_{A}:\;{µ}_{tDCS}\;-\;0.5\;{µ}_{placebo}\;-\;0.5\;{µ}_{drug}>\;0$$

In a non-inferiority triple-arm trial, there are three relevant comparisons: (1) experimental treatment versus active comparator (i.e. tDCS versus escitalopram); (2) experimental treatment versus placebo; and (3) active comparator versus placebo. Authors such as Koch and Röhmel^29^ have considered that the third comparison is not strictly necessary if the former two were significant, but in their approach, two or three null hypotheses would have to be independently rejected (thereby decreasing the P value), or the trial would only be valid if all hypotheses were rejected.^30^ Therefore, we use here an alternative model presented by Pigeot et al.^31^ and already used in the literature,^32^ in which the study aim can be presented in a single H_0_, which simultaneously tests the non-inferiority between active treatments and their superiority against placebo, thereby decreasing the number of multiple comparisons.

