## CONCLUSIONS

The ELECT-TDCS trial is a 10-week, phase-III, non-inferiority, triple-arm, placebo-controlled study that is investigating whether tDCS is non-inferior (i.e. whether it has similar or superior efficacy) to 20 mg/day of escitalopram. The results from our trial have the potential to introduce a novel technique into the therapeutic arsenal for depression treatment, particularly in primary care contexts or among patients who cannot tolerate or are not willing to use antidepressant drugs. Our multimodal investigation of biomarkers will also contribute towards understanding the antidepressant mechanisms of the effects of tDCS.

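### The primary test can show only that tDCS keeps more than half of the escitalopram effect, but the article equates a positive result with similar or superior efficacy

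*Protocol article*

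**What the plan says.** **What is tested.** In the Overview of the Methods, improvement is the change from baseline to endpoint, and the alternative is that tDCS minus placebo exceeds half of escitalopram minus placebo: "The study’s primary aim is to prove the alternative hypothesis, i.e. that this difference is greater than 50" per cent. The Abstract says the same: "with a non-inferiority margin of at least 50% of the escitalopram effect, in relation to placebo". The Design and sample size section sets M2/M1 = 0.5, with M1 the escitalopram-placebo difference seen in this trial, so "it will be known only when the study has been finished". It adds that non-inferiority will be accepted only if the mean escitalopram-tDCS difference is under 3 HDRS-17 points. The Statistical analysis section gives the matching one-sided t test.

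**What a positive result is said to mean.** The Design and sample size section: "Our aim is to prove that tDCS is non-inferior (i.e. that it has similar or superior efficacy) to escitalopram". The Conclusions: "non-inferior (i.e. whether it has similar or superior efficacy) to 20 mg/day of escitalopram". In both places the definition hangs on an 'i.e.', so it explains what non-inferior means in this trial.

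**The concern.** A treatment that gives up nearly half of the drug's benefit over placebo still lies inside the alternative hypothesis. Calling it similar is a stronger statement than the test makes, and calling it superior is a different statement altogether, because the primary test contains no superiority step against escitalopram.

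What is at stake is the sentence a reader takes away. The article anticipates use in primary care and in patients who cannot or will not take antidepressants. Such readers would understand the conclusion as parity with a full-dose first-line drug, when the formal evidence is a lower bound of one half.

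**Working it through.** **Inputs.** From the Design and sample size and Statistical analysis sections: f = 0.5; SD ratio ε = 1.5 (SD divided by the drug-placebo difference D); arms of 90 tDCS, 90 escitalopram and 60 placebo; one-sided α = 0.025; critical t = 1.97 on 237 df; 3-point condition. The documents give no value for D in points, so a range is assumed wherever points are needed.

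**1. The plan's own figures.** √(1/90 + 0.25/90 + 0.25/60) = √0.018056 = 0.13437, and 1/0.13437 = 7.44, as printed. The 97.5% point of t on 237 df is 1.970, as printed.

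**2. What rejection bounds.** When T equals 1.97, the value of f that is only just not rejected is 0.5. So, where escitalopram itself separates from placebo, the one-sided 97.5% lower bound on retention at the threshold is 50%.

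**3. How often a weaker tDCS passes.** For true retention r, the noncentrality is 7.44 × (r − 0.5)/1.5, and the chance of passing is P(T > 1.97) from the noncentral t on 237 df.

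| True retention r | Noncentrality | Chance of passing |
|---|---|---|
| 60% | 0.50 | 7.1% |
| 70% | 0.99 | 16.6% |
| 75% | 1.24 | 23.4% |
| 80% | 1.49 | 31.6% |
| 100% | 2.48 | 69.5% |

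With 13% attrition (78/78/52) the figures at 60%, 75% and 80% are about 7%, 21% and 28%.

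**4. What the 3-point condition adds.** The 50% margin in points is 0.5 × D, so the condition is tighter only when 0.5 × D > 3, that is D > 6. For D from 2 to 8 points (assumed) and ε = 1.5, simulation shows that the condition lowers the chance of declaring non-inferiority by at most about 0.2 percentage points.

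**5. What a just-significant result looks like at the planned ratio.** If the observed ratio is 1.5, T > 1.97 requires observed retention above 0.5 + 1.97 × 1.5/7.44 = 0.897, about 90%. The observed deficit at that point is about 0.10 × D, or 0.3 to 0.6 points for D of 3 to 6 (assumed). The 95% CI for the tDCS-escitalopram difference has half-width 1.97 × 1.5 × √(2/90) × D = 0.44 × D. The limit against tDCS is therefore about (0.10 + 0.44) × D = 0.54 × D, or 1.6 to 3.3 points over the same range of D.

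**6. When the SD ratio is smaller.** The plan says ε can lie between 0.2 and 2. The retention test passes if observed retention exceeds 0.5 + (1.97/7.44)ε = 0.5 + 0.265ε. Escitalopram is significantly better than tDCS if observed retention is below 1 − 1.97√(2/90)ε = 1 − 0.294ε. Both can hold when 0.559ε < 0.5, that is ε below about 0.90.

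Illustration (assumed): D = 6, SD = 4.2 (ε = 0.7), observed retention 75%.
- Retention test: T = 7.44 × 1.5/4.2 = 2.66, a pass.
- Observed deficit: 1.5 points, under the 3-point condition.
- Escitalopram against tDCS: t = 1.5/(4.2 × 0.149) = 2.40, significant in favour of escitalopram.

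In simulation at that ratio with true retention 75%, all three occur together about 42% of the time. At ε = 1.5 the joint result is below 0.1%.

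**The case against.** The strongest reply is that nothing is hidden or miscalculated. The 50% criterion stands in the Abstract, the formal hypotheses, the margin section and the test statistic, and a non-trivial chance of rejecting just inside the alternative is a property of every non-inferiority test. The plan also gives 'similar' some clinical content through the 3-point condition, which it ties to a clinically meaningful difference. At the planned SD ratio a success would show a point estimate close to escitalopram. All of this stands, and it limits the point to how the result is described.

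Three stronger readings are tempting, and the documents do not support them.
- *The design cannot support any claim of similarity or superiority.* The three-arm data give an estimate and a confidence interval for tDCS against escitalopram, and the Statistical analysis section plans exploratory mixed-model ANOVAs with post-hoc analyses that could compare the two. It is the primary test that does not deliver the claim.
- *A clearly weaker tDCS would be reported as similar.* At 60% retention the test fails about 93% of the time, and at 75% about 77%.
- *The plan declares equivalence as its conclusion.* The phrase "but in fact due to true equivalence between treatments" belongs to an argument about assay sensitivity, and "Proving that tDCS is similarly effective to antidepressants would have a tremendous impact on clinical psychiatry" is motivation. Neither is a decision rule. Only the two definitions of non-inferiority carry the point.

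The reply does not remove the mismatch. As worded, the 3-point condition concerns the mean difference and sets no confidence limit, so it does not turn a 50% lower bound into evidence of similarity. Nor is this a detail left to an analysis plan: the article itself fixes both the hypothesis and the label.

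**Conclusion.** The point holds as a mismatch between label and test. A positive primary result supports retention of more than 50% of the escitalopram-placebo effect with an observed mean difference below 3 HDRS-17 points. It does not by itself support similar efficacy, and it does not address superiority over escitalopram.

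On the plan's inputs, a tDCS that truly loses a quarter of the effect earns the label about 23% of the time. This assumes 240 analysed patients and an SD ratio of 1.5. If the true ratio is well below 0.9, which the plan's stated range allows, the rule can often be met while escitalopram is significantly better; at the planned ratio that is negligible. Statements in points rest on an assumed drug effect.

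The wording should be corrected before results are reported, because it governs what the trial may conclude. The test and the margin are not at fault on this point. The 69.5% chance of passing at full retention, against the planned 80%, concerns the sample size and is a separate matter.

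**What to change.** - In the Design and sample size section and in the Conclusions, replace the similar-or-superior definition with the tested claim: *tDCS retains more than 50% of the escitalopram-placebo effect, with an observed difference below 3 HDRS-17 points*.
- Report the tDCS-escitalopram difference with its 95% CI beside the primary test.
- Claim superiority over escitalopram only if that interval excludes zero in favour of tDCS.

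The test, margin, allocation and sample size stay as they are, and no further patients or assessments are needed. The cost is two changes of wording, one confidence interval and a more modest headline claim.
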